## Abstract

**Introduction:**

Therapeutic physical exercise (TPE) is considered the cornerstone intervention to prevent or reverse frailty; however, prefrail individuals often face challenges achieving the exercise intensity required to induce multisystem adaptations. Non-invasive neuromodulation techniques—including virtual running–based visual illusion (VR) and, transcranial direct current stimulation (tDCS),—have shown promising effects on neuroplasticity, motor performance and executive function. The primary objective of this study is to compare the effect of adding two neuromodulation strategies to a multicomponent TPE programme on functional capacity and quality of life in prefrail older adults.

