Although VR and tDCS both aim to enhance neuroplasticity, they are expected to act through partially distinct neural pathways. VR-based visual illusion primarily engages the action-observation network and mirror neuron system, involving premotor cortex, inferior parietal cortex and sensorimotor integration networks (Kim and Lee, 2021). Conversely, anodal tDCS induces subthreshold modulation of neuronal membrane potentials, facilitating Hebbian plasticity, NMDA-receptor activity and BDNF-dependent synaptic strengthening (Fritsch et al., 2010). Consequently, these interventions may produce distinct neurophysiological adaptations and functional outcomes.

Although several studies have demonstrated additive benefits of combining exercise with neuromodulation techniques in various, these approaches have generally been investigated independently and focused primarily on cognitive aspects, rather than functional. To our knowledge, no randomized controlled trial has directly compared the effect of VR and tDCS when added to a multicomponent exercise programme in parameters related to functional capacity and quality of life in prefrail individuals.

Therefore, this study hypothesizes that adding any of these two therapies (VR and tDCS) to a multicomponent TPE intervention programme will result in additional improvements in parameters related to functional capacity and quality of life in prefrail individuals. This will contribute to preventing the progression toward frailty and, therefore, reducing the social and healthcare costs associated with this condition.

**Objectives:** The general objective of this study is to evaluate the effectiveness of non-invasive neuromodulation combined with a multicomponent TPE programme on variables related to functional capacity and quality of life in prefrail older adults. As specific objectives, the current study seeks to determine the effect of two neuromodulation strategies (i.e., tDCS and VR) combined with a multicomponent TPE programme on gait speed, general physical condition, frailty, static and dynamic functionality and gait quality, upper limb and lower limb isometric strength, quality of life, and neuroplasticity, in terms of plasma BDNF levels, in prefrail older adults.

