### Design and setting

2.1

This protocol describes a four-arm triple-blinded (participant, outcome assessor, statician) randomised controlled trial that will be conducted in the Faculty of Physiotherapy (University of Valencia). The participants will be randomly allocated into four groups that will be described later: (i) VR + TPE; (ii); sham VR + TPE; (iii) tDCS + TPE and (iv) sham tDCS + TPE. Assessments will be conducted at the following time points: before the first session (T1), immediately after the first session (T2), after 4 weeks of intervention (T3), immediately after the 8-week intervention period (T4) and at 4 week-follow-up (T5). This longitudinal assessment schedule is necessary given the nature of the intervention, which is hypothesized to induce both immediate and experience-dependent neuroplastic changes over time. Early time points (T1–T2) allow the capture of acute neurophysiological and behavioral effects following initial exposure, whereas intermediate and post-intervention assessments (T3–T4) are essential to evaluate progressive training-related adaptations. Finally, the follow-up assessment (T5) enables the examination of the retention and consolidation of treatment-induced effects, providing insight into the durability of potential neuroplastic reorganization. The study design is in accordance with the 2025 Standard Protocol Items: Recommendations for Interventional Trials (SPIRIT) statement (Chan et al., 2025). The flow chart of the study is shown in Figure 1.

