### Statistical analysis

2.9

Data analysis will be performed using the statistical program SPSS v29. For all studies, sample normality will be analysed using the Shapiro Wilk test, homoscedasticity using Levene’s test, and sphericity for the intra-subject factor using Mauchly’s test. For the comparison between groups, a mixed- design ANOVA will be used, with the between-subjects factor “group” (with the two groups included in each sub-study) and the intra-subject factor “time” including the five assessments. The dependent variables will be those described in the variable description section. The Bonferroni correction will be used for *post-hoc* comparisons. If there is a potential confounding factor that meets the requirements (independence and homogeneity of the lines) to be analysed as a covariate, ANCOVA will be used. The possible heterogeneity of the samples from each pair of groups (in each sub-study) in the baseline will be analysed using an independent samples One-way ANOVA. Differences will be considered statistically significant when the *p*-value is less than 0.05.

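### The abstract and introduction promise a VR-versus-tDCS comparison, but section 2.9 analyses two groups per undefined sub-study and specifies no such contrast

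*Protocol article*

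**What the plan says.** The protocol article describes its aim in two ways.

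- **Comparison of techniques.** Abstract, Introduction: "The primary objective of this study is to compare the effect of adding two neuromodulation strategies to a multicomponent TPE programme". Section 1 (Introduction) then says that, to the authors' knowledge, "no randomized controlled trial has directly compared the effect of VR and tDCS when added to a multicomponent exercise programme" in this population, and argues that the two techniques may lead to different adaptations and outcomes.
- **Added effect of each technique.** The hypothesis in section 1 is that "adding any of these two therapies (VR and tDCS) to a multicomponent TPE intervention programme will result in additional improvements". The specific objectives say the study "seeks to determine the effect of two neuromodulation strategies (i.e., tDCS and VR) combined with a multicomponent TPE programme". Neither asks which technique is better.

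Section 2.1 randomises participants once, to four arms: VR+TPE, sham VR+TPE, tDCS+TPE and sham tDCS+TPE. Section 2.9 gives the between-subjects factor only two levels per model, "with the two groups included in each sub-study", and checks baseline balance pair by pair in the same way. The term sub-study occurs only in section 2.9. Neither the number of sub-studies nor which arms form each pair is stated.

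**The concern.** If each sub-study is an active arm against its own sham, which is the natural reading with technique-specific shams, no planned test or interval sets VR against tDCS. The Bonferroni post-hoc comparisons do not help, because a correction inside a two-group model cannot reach an arm that is not in the model.

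The comparison announced in the abstract could then be made only by setting one sub-study's p-value beside the other's. That is not a valid comparison: one significant and one non-significant result is not evidence that the effects differ. At this sample size such a split is common even when the two effects are identical, and a reader told that the trial compares the techniques could take it as a ranking.

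**Working it through.** **1. Inputs.** Section 2.7 gives a difference of 0.19 m/s, SD 0.29 m/s, 5% type I error, 80% power, 16 per group before losses and 20 after. Assumed here, because not stated: two-sided tests, equal allocation, and one post-treatment walking-speed score as the outcome.

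**2. The plan's own figure.** The dropout step reproduces: 16/0.8 = 20, and 4 × 20 = 80. The 16 does not follow from the stated inputs as a two-group comparison: d = 0.19/0.29 = 0.655 needs 38 per group by a two-sided t test. The article does not name the test behind the 16, so it is not used as evidence here. Only the arm sizes 16 and 20 are carried forward.

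**3. Power of one active-versus-sham sub-study.** Noncentral t with 2n − 2 degrees of freedom and noncentrality 0.19/(SD × √(2/n)).

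- n = 16: SE = 0.29 × √(2/16) = 0.1025; noncentrality 1.85; power 43%.
- n = 20: SE = 0.29 × √(2/20) = 0.0917; noncentrality 2.07; power 52%.

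**4. Chance that exactly one of two sub-studies is significant when both effects are 0.19 m/s.** The pairs share no participants, so the chance is 2p(1 − p).

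- n = 16: 2 × 0.434 × 0.566 = 49%.
- n = 20: 2 × 0.524 × 0.476 = 50%.

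This formula cannot exceed 50%. Even at the planned 80% power it gives 2 × 0.8 × 0.2 = 32%.

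**5. Precision of the sham-corrected contrast,** (VR − sham VR) − (tDCS − sham tDCS). SE = SD × √(4/n), with 4n − 4 degrees of freedom.

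- n = 16: SE = 0.29 × √(4/16) = 0.145; 95% half-width 0.29 m/s; power 25% for a true difference of 0.19 m/s.
- n = 20: SE = 0.29 × √(4/20) = 0.130; half-width 0.26 m/s; power 30%.

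**6. Sensitivity to the SD.** Section 2.7 does not say what kind of SD 0.29 m/s is, and section 2.9 includes baseline among the five assessments. If 0.29 is a single-score SD and baseline is adjusted for with correlation ρ, the SD becomes 0.29 × √(1 − ρ²). The values of ρ are assumptions.

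| ρ | n per arm | Power, one sub-study | Exactly one significant | Power, difference of differences | 95% half-width (m/s) |
|---|---|---|---|---|---|
| 0 | 16 | 43% | 49% | 25% | 0.29 |
| 0 | 20 | 52% | 50% | 30% | 0.26 |
| 0.5 | 16 | 54% | 50% | 32% | 0.25 |
| 0.5 | 20 | 64% | 46% | 39% | 0.22 |
| 0.7 | 16 | 71% | 41% | 44% | 0.21 |
| 0.7 | 20 | 81% | 31% | 53% | 0.18 |
| 0.8 | 16 | 85% | 26% | 57% | 0.17 |
| 0.8 | 20 | 92% | 15% | 67% | 0.16 |

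**7. The simpler direct contrast.** VR+TPE against tDCS+TPE is also a randomised comparison. Unadjusted, it has the power in step 3: 43% at 16 and 52% at 20 per arm.

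**The case against.** Own-sham comparisons do answer the main-text hypothesis and specific objectives, and the Discussion also frames success as either technique measured against exercise alone. The abstract sentence is loose enough to mean added versus not added, and the sentence about the missing direct comparison is a statement of a gap, not an objective. All of that stands. A reader might infer that the trial cannot answer its main question, but that goes too far: the plan can address each technique's added effect. What these points do not explain is why the article claims a direct comparison as its novelty.

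A reader might also infer that the protocol fixes exactly two sub-studies, each active arm against its own sham, and so rules out a VR-versus-tDCS test. The text does not say so. The pairing is an inference, and a VR/tDCS pair is not excluded. The supportable statement is that the sub-studies are undefined and that no such contrast is specified.

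The 49-50% figure depends on treating 0.29 m/s as an unadjusted SD. With strong baseline correlation it falls to as little as 15%, so a range is needed. The contrast itself stays below 80% power throughout that range.

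Deferral to a separate analysis plan does not dispose of the point: the article states the model and the number of groups in it, and that statement does not match the comparison announced in the abstract and introduction.

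**Conclusion.** The point holds as an inconsistency between objectives and analysis. The abstract objective and the introduction's rationale call for a VR-versus-tDCS comparison, the hypothesis and specific objectives do not, and section 2.9 specifies none.

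If readers fall back on comparing significance across sub-studies, equal true effects of 0.19 m/s would give one significant and one non-significant result about 49-50% of the time (16-20 per arm, SD 0.29 m/s unadjusted), or about 15-50% with an assumed baseline correlation of 0.5-0.8. A sham-corrected contrast would have 25-30% power unadjusted and about 32-67% under those correlations. These figures rest on two-sided tests, active-versus-own-sham pairing and walking speed only. They say nothing about the other primary outcome, frailty status, which is categorical.

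Randomisation, arms and data collection are unaffected.

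**What to change.** Either of two text changes, made before unblinding, resolves it.

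1. **Keep the comparison.** State how many sub-studies there are and which arms each contains. Fit one model with all four arms and pre-specify, at a named time point, VR minus sham VR, tDCS minus sham tDCS, and a VR-versus-tDCS contrast such as the difference between those two differences. Report the last as an estimate with 95% CI, labelled as not powered and kept outside the confirmatory tests. State how multiplicity is handled for the two active-versus-sham contrasts. Frailty status needs the matching contrasts on a scale suited to a categorical outcome.
2. **Drop the comparison.** Remove the direct-comparison wording from the abstract objective and the introduction, and state the objective as two separate active-versus-sham comparisons. The sub-studies should still be defined.

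The first option needs no new data. At 20 per arm it raises the error degrees of freedom from 2 × 20 − 2 = 38 to 4 × 20 − 4 = 76. Its small downside is the assumption of similar variance across arms. The second costs only the novelty claim.

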**Methods and analysis:**

This four-arm, triple-blinded randomized controlled trial will include adults aged ≥ 65 years classified as prefrail according to Fried criteria. Participants will be randomly assigned to one of the following groups: VR+TPE, sham VR+TPE, tDCS+TPE or, sham tDCS+TPE. All interventions will be applied during an 8 week-programme consisting of 24 supervised sessions. The primary outcomes will be frailty status (Fried Phenotype) and walking speed. Secondary outcomes will include neuroplasticity biomarkers (plasma BDNF), heart rate variability, upper and lower limb isometric strength, quality of life (EQ 5D 5L), lower-limb muscle power, static and dynamic functionality, gait quality and dual-task performance. Assessments will be conducted at baseline, immediately after the first session, at 4 weeks, at the end of the 8 week intervention, and at 4 week follow up.

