### Participants

2.3

Participants aged over 65 years will be recruited through different older people’s associations (i.e., La Nau Gran and Asociación Grupo de Mayores de Telefónica). The study will also be advertised on the research group website and social media. The researchers will establish compliance with the selection eligibility criteria described in Table 1. Researchers may terminate a participant’s involvement in the study if changes in the participant’s clinical status result in non-compliance with the established eligibility criteria.

**TABLE 1 T1:** Eligibility criteria.

Eligibility Criteria	
**Inclusion criteria**	**1. Exclusion criteria**
Aged over 65 years	History of stroke within the past 6 months or hospital admission for any reason within the past 3 months
Being prefrail according to Fried criteria	Diseases of the central or peripheral nervous system
Ability to understand instructions (Mini-Mental State Examination > 23 points)	Vestibular system
Signing the written informed consent.	Concomitant diseases Have a neurological pathology, cardiovascular musculoskeletal that contraindicates physical activity Epilepsy or history, medications that lower the seizure threshold Cardiac pacemaker, endocranial and hearing implants History of severe headaches Uncontrolled intracranial or arterial hypertension Heart and/or respiratory failure Implanted medication pump Skin lesions (psoriasis, eczema) Serious head surgeries Completing less than 80% of training sessions

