##### Frailty condition

2.5.1.1

Frailty status will be assessed using the Fried Frailty Phenotype. Participants will be classified as frail if they meet three or more of the following criteria: (i) unintentional weight loss greater than 4.5 kg in the previous year; (ii) self-reported exhaustion; (iii) low level of physical activity; (iv) slowness, determined by gait speed; and (v) muscle weakness, assessed by handgrip strength. Participants meeting one or two criteria will be classified as pre-frail, whereas those meeting none of the criteria will be considered robust. The Fried Frailty Phenotype has demonstrated good predictive validity and reliability for adverse health outcomes in older adults (Fried et al., 2001).

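### Frailty status, a co-primary outcome with three classes and no variation at baseline, is assigned a five-visit mixed ANOVA whose result does not say how many participants became robust or frail

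*Protocol article*

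**What the plan says.** The Abstract states that "The primary outcomes will be frailty status (Fried Phenotype) and walking speed". Section 2.5.1.1 defines frailty status purely as a classification. On the upper class it says "Participants will be classified as frail if they meet three or more of the following criteria", and on the other two "Participants meeting one or two criteria will be classified as pre-frail, whereas those meeting none of the criteria will be considered robust". It does not say that the 0 to 5 count of criteria is the variable to be analysed. Table 1 in section 2.3 lists "Being prefrail according to Fried criteria" among the inclusion criteria.

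Section 2.9 says that a "mixed- design ANOVA will be used" for the comparison between groups, with the two groups of each sub-study as one factor and all five assessments as the other. It then adds "The dependent variables will be those described in the variable description section". No outcome is excepted. The same section plans Shapiro-Wilk, Levene and Mauchly tests and a one-way ANOVA at baseline. The only alternative it names is ANCOVA, which is also a normal-theory model. It gives no categorical method and no fallback if a check fails.

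**The concern.** The model named for this primary outcome assumes a continuous, roughly normal response. The outcome has three ordered classes, and eligibility fixes it at the middle class for everyone at T1. The protocol is not silent here in a way that an analysis plan could fill: it states a method, and that method does not suit the outcome. An analysis plan that followed section 2.9 would inherit the problem, and one that departed from it would contradict the published protocol on a primary outcome.

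What is at stake is what the trial can report. The Introduction and Discussion describe prefrailty as reversible and name preventing progression toward frailty as a purpose. A reader will want to know how many more participants became robust, and how many became frail, on active treatment than on sham. A group-by-time F-test on category codes answers neither question.

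**Working it through.** **Inputs.** Three classes (section 2.5.1.1), coded here 0 = robust, 1 = prefrail, 2 = frail. All participants prefrail at T1 (Table 1). Two groups by five visits (section 2.9). 16 per group, or 20 after allowing for 20% loss: 16 / (1 − 0.20) = 20 (section 2.7). Section 2.7 bases these on walking speed (0.19 m/s, SD 0.29 m/s). The protocol gives no sample-size figure and no expected rates for frailty status, so all rates below are assumptions.

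**1. Planned checks at T1.** Every value is 1, so the between-group and within-group sums of squares are both 0 and F = 0/0. Run on constant data, one-way ANOVA and Levene's test return no number, and Shapiro-Wilk returns only a placeholder (statistic 1, p = 1).

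**2. Mauchly's test.** In simulation (4,000 runs per scenario), the contrast covariance matrix was singular in every run if frailty status was also constant at T2. If a few participants changed at T2, it was singular in 13 to 19% of runs.

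**3. Normality after baseline.** In samples of 20 drawn from an assumed 35/60/5% split, Shapiro-Wilk rejected normality in all 2,000 samples.

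**4. False-positive rate.** The two-group, five-visit ANOVA was simulated on the 0/1/2 code with no group difference, under three assumed patterns and at 16 and 20 per group:

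| Test | Type I error at nominal 5% |
|---|---|
| Group by time, uncorrected | 6.0 to 8.0% |
| Group by time, Greenhouse-Geisser | 3.4 to 4.7% |
| Group main effect | 4.0 to 5.5% |

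**5. What the mean code conveys.** Mean = 0 × P(robust) + 1 × P(prefrail) + 2 × P(frail).
- Arm with 25/75/0%: 0.75 + 0 = 0.75.
- Arm with 35/55/10%: 0.55 + 2 × 0.10 = 0.75.

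The means are equal, yet 0% of one arm and 10% of the other became frail. An extreme case is 0/100/0% (mean 1.00) against 30/40/30% (0.40 + 0.60 = 1.00). With those rates at T3 to T5 and 20 per group, the ANOVA rejected in about 5% of runs.

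**6. Power for robust at T4.** Unadjusted two-proportion z-test, pooled variance, two-sided 5%, exact enumeration:

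| Assumed robust, sham v active | 16 per arm | 20 per arm |
|---|---|---|
| 30% v 50% | 22% | 25% |
| 30% v 60% | 41% | 46% |
| 30% v 70% | 65% | 71% |
| 10% v 50% | 76% | 84% |

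**The case against.** A reader might infer that the planned ANOVA cannot give a valid test at all. The documents and the simulation do not support that. Step 4 shows error rates near the nominal level with a sphericity correction and only modestly above it without one. The undefined T1 tests also do no harm to the treatment comparison itself: if everyone shares one baseline value, there is no imbalance in that value to find. This part of the objection stands, and the point does not rest on false positives.

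A reader might also infer that frailty status cannot change at all by T2, straight after the first session. The look-back, "unintentional weight loss greater than 4.5 kg in the previous year", belongs to one criterion of five. Gait speed and grip strength can differ after a session, and section 2.1 gives a rationale for T2 in terms of acute effects. The look-back supports treating T2 frailty status as descriptive, and no more than that.

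The 30/40/30% example is constructed. All four arms receive 24 supervised exercise sessions, and nothing in the protocol suggests such rates. A rank-based ordinal test would largely miss the same difference (about 8 to 9% rejection). The example shows why both proportions must be reported; it does not show that the ANOVA would be uniquely blind.

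Finally, walking speed, the variable used for the sample size, is continuous, and an ANOVA suits its scale. That is true, but frailty status is declared primary beside it, and no passage supplies another method for it.

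**Conclusion.** The point holds as a mismatch between a stated method and a primary outcome. Three facts carry it, all in the protocol: the outcome is defined only as three classes, it is constant at T1 by eligibility, and section 2.9 applies one normal-theory model to every outcome. Two planned baseline procedures are undefined for it, normality cannot hold, and the estimate has no reading as participants recovered or progressed.

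The size of the problem lies in interpretability, not in error control. The simulated type I errors depend on assumed transition rates and an assumed within-person correlation. The power figures depend on assumed rates and an unadjusted test, and they range from 22% to 84%. They show that power for frailty status is not assured at this sample size; they do not measure a loss caused by the ANOVA.

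**What to change.** In section 2.9, keep the mixed ANOVA for continuous outcomes only. For frailty status:
- Pre-specify one primary post-baseline time, for example T4, and compare each active arm with its own sham, adjusting for the baseline number of Fried criteria (1 or 2). Leave T1 out of the response.
- Use either a proportional-odds model on robust/prefrail/frail, or robust yes/no with the risk difference and 95% CI, stating how the adjusted risk difference is obtained. The ordinal model keeps both directions of change; the binary endpoint is simpler to read but ignores progression.
- In either case, report by arm both the proportion becoming robust and the proportion progressing to frail.
- Treat T2 frailty status as descriptive.
- Show the 0 to 5 count of criteria as a supporting analysis.

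In section 2.7, state that the sample size was set on walking speed only and gives no assured power for frailty status.

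The cost is analysis wording: visits and measurements are unchanged. The downside is limited power from a categorical endpoint at 16 to 20 per arm, which should be stated openly. The change should be made before any unblinded analysis, because a method chosen later for a primary outcome would be post hoc.
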